### Outcomes

All outcome measures are listed in Table 1 and mediator measures in Table 2. Measures were selected following a comprehensive literature search and consultation with experts in diet and physical activity. Evidence of reliability, validity and sensitivity to change were considered in the selection process. An important issue was completion time to avoid excessive respondent burden as this could affect follow-up rates. For most of the outcomes and for the mediators there was a limited choice of measures and the final choice was inevitably a compromise between evidence of good psychometric properties and the resources and time available to complete the assessments.

**Table 1 T1:** Measurement of Outcomes

**Outcomes**	**Measure**	**When***
**Primary outcome**		
Maternal weight expressed as BMI relative to height measured at baseline	Calibrated adult scales & stadiometer	B, 36w, 6p, 6 m, 12 m
**Secondary outcomes**		
Antenatal and birth complications**	Routinely collected data held in patient records	Birth
Pregnancy weight gain	Calibrated adult scales	B, 36w
Waist circumference and waist-hip ratio	Measuring tape	12 m
Child weight centile (adjusted for birth weight and age)	Calibrated baby scales and measuring tape	Birth, 6p, 6 m, 12 m
Admission to neonatal unit	Patient records	Birth
General mental health	General Health Questionnaire (GHQ) 12 [82]	B, 36w, 6p, 6 m, 12 m
Breast feeding intentions	Study-developed questions	36w
Breast feeding behaviour and weaning	Study-developed questions	6p, 6 m, 12 m
Self-reported physical activity	7 Day Physical Activity Recall (7 Day PAR) [83-85]	B, 36w, 6p, 6 m, 12 m
Diet	Dietary Instrument for Nutrition Education (DINE) [86] (plus additional questions on fruit and vegetables, sugar, sweets)	B, 36w, 6p, 6 m, 12 m
Alcohol	Alcohol Use Disorders Identification Test-Consumption (AUDIT-C) [87]	B, 36w, 6p, 6 m, 12 m
Smoking	Study-developed questions	B, 36w, 6p, 6 m, 12 m
Costs	Participant resource use	B, 36w, 6p, 6 m, 12 m
Health related quality of life	EQ-5D (including visual analogue scale) [88]	B, 36w, 6p, 6 m, 12 m

*B = baseline; 36w = 36 weeks gestation; 6p = 6 weeks postpartum; 6 m = 6 months postpartum; 12 m =12 months postpartum.

**gestational diabetes; pre-eclampsia; thrombosis; proportion staying within IOM guidance on weight gain in pregnancy [20]; form of pain relief; birth delivery mode; gestation at delivery; induction of labour; shoulder dystocia, 3^rd^/4^th^ degree perineal tear; postpartum bleeding or thrombosis; Apgar scores.

**Table 2 T2:** Measurement of Mediators

**Mediators**	**Measure**	**When**
Social support	Social Support Exercise and Eating Habits Scales [89] (plus intervention specific social support questions)	B, 36w, 6 m, 12 m
Self-efficacy	Weight Efficacy Lifestyle Scale [90] and Multidimensional Self efficacy for Exercise Scale [91,92]	B, 36w, 6 m, 12 m
Self-regulation	Shortened Self-Regulation Questionnaire [93]	B, 36w, 6 m, 12 m
Motivation	Treatment Self-Regulation Questionnaire (for diet and physical activity) [94]	B, 36w, 6 m, 12 m

(B = baseline; 36w = 36 weeks gestation; 6 m = 6 months postpartum; 12 m =12 months postpartum).

The primary outcome is maternal BMI at 12 months postpartum. Secondary outcomes will include investigation into the impact of the intervention on gestational weight gain, the child’s weight gain, complications during pregnancy, at birth and postnatally, diet, physical activity levels, health related quality of life, mental health and breast feeding intentions. All staff collecting data will be trained in administering the different outcome measures as well as accurately measuring weight, height and waist and hip circumference. Height will be measured once at baseline and used for all BMI calculations.

Information on both adverse events (AE) and serious adverse events (SAE) will be collected in the study. Trial sites, participants’ GPs and intervention staff are responsible for reporting AEs and SAEs. They may also be reported by participants and by staff completing follow-up. In this trial cohort the following are expected to occur: hospitalisation for normal birth or any antenatal, perinatal or postnatal complications, termination of pregnancy for foetal anomaly and hospitalisation for postnatal depression. Rates of AEs and SAEs are likely to be higher in this group of obese women than the normal population of pregnant women. There are no SAEs expected to be related to the study intervention.

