## Background

### Obesity: the problem

The Foresight Report (2007) estimates by 2050, 50% of women could be obese and National Health Service (NHS) costs associated with obesity could be £10 billion per annum [1]. Approximately 1 in 5 women attending antenatal care in the United Kingdom (UK) are obese [2,3] and this figure is likely to increase. In Europe and the United States of America (US) between 20 and 40% of women gain more weight during pregnancy than is routinely advised [4]. Pregnancy is a significant factor in the development of obesity in women. Many women retain cumulative weight gained over several pregnancies and women with high weight gain during pregnancy retain more weight at follow-up [5-7]. Excess maternal weight gain during pregnancy is also associated with child obesity at 3 years and in adolescence [8,9]. This suggests there is potential for influencing the mother’s lifestyle and weight as well as the child’s weight.

Obesity has been linked to an increased risk of complications during pregnancy and birth including pregnancy-induced hypertension [2,10], gestational diabetes mellitus [2,11], increased emergency and elective caesarean section rates [2,10], increased induction of labour rates [2,11], venous thromboembolism [12] and increased postpartum haemorrhage [2,13]. There are also increased risks for the child including pre-term birth [2,11], shoulder dystocia [14], admission to a neonatal unit [2,13], birth defects (e.g. spina bifida, omphalocele) [14], still birth [2,13], macrosomia [2,15], fetal and neo-natal death and poor Apgar scores [16]. Consequently, the NHS costs are significantly higher in overweight and obese pregnant women compared to women in the normal weight range. Antenatal care costs may be 5–16 times higher in overweight and obese women [2,17].

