With regard to pregnant obese or overweight women, a recent large randomised controlled trial (RCT) found no impact of a lifestyle intervention on gestational weight gain (GWG) or on the proportion of women whose weight gain was below or within IOM guidance [32]. The intervention did not reduce the risk of large for gestational age infants nor did it improve maternal outcomes. However, the intervention was associated with a reduction in the risk of birth weight above 4000 g. A recent high quality meta-analysis of RCTs of interventions of diet and physical activity, alone or in combination, which included studies where women were obese, overweight and normal weight, found an overall 1.42 kg difference between intervention and control participants in GWG (in favour of the intervention group) [33]. For diet alone the difference was 3.84 kg. For interventions targeting obese or overweight women only the reduction in GWG was 2.1 kg. This review also found that reductions in pregnancy weight gain were not associated with an increased rate of small for gestational age babies. Interventions were associated with a lower risk of pre-eclampsia and shoulder dystocia and there was a trend towards a reduction in gestational diabetes, gestational hypertension and pre-term birth. However, the quality of the evidence was low for clinical outcomes as there was evidence of significant heterogeneity in the effect size, study level biases including issues with randomisation, incomplete outcome data, blinding, as well as risk of publication bias [33]. Other systematic reviews and meta-analyses have also found lower GWG from diet and physical activity interventions, but included studies often had methodological limitations including high loss to follow-up, small sample sizes and problems with blinding [34-38]. A Cochrane review of interventions to prevent excessive weight gain during pregnancy concluded that due to small effect sizes and methodological limitations of studies no intervention could be recommended for limiting excessive GWG [39].

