### Aim of the study

The primary aim is to assess whether a weight management intervention for obese pregnant women is effective in reducing the women’s Body Mass Index (BMI) 12 months after giving birth.

Secondary aims include:

•to examine whether the intervention leads to lower weight gain during pregnancy;

•to assess whether the intervention leads to fewer complications during pregnancy, at birth and postnatally;

•to examine the impact of the intervention on diet, physical activity levels, health related quality of life, mental health, self-efficacy, social support and breast feeding;

•to examine the child’s weight gain;

•to examine mediators and moderators of change;

•to conduct a cost effectiveness analysis;

•to conduct a process evaluation to examine participant views, drop out, fidelity, duration of participation in the intervention and associated factors.

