### Study intervention

A logic model (shown in Figure 1) describing the theory of the intervention was developed. This illustrates the key inputs, outputs/behaviours and outcomes of the intervention. Participants attending intervention sites will have the opportunity to attend free, weekly, 1.5 hour weight management group sessions from the point of recruitment (between 12 and 20 weeks gestation) up until 6 weeks postpartum. At this time point they will receive one voucher for a free Slimming World session at a ‘normal’ community group. They will also receive two intervention phone calls from the Intervention Midwife at 3 and 6 months postpartum in order to provide longer term support and encouragement. Long term intervention contact helps sustain weight loss [61] and telephone support can be effective in weight loss interventions [62]. Assuming normal gestation of between 37 and 42 weeks and depending on when women were recruited, the intervention period will be up to 56 weeks in total.

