### Site randomisation

Sites will be randomised when all necessary approvals are obtained. Randomisation will be completed to give optimal balance for geographic region, maternity unit size, ethnic mix and the proportion of the maternity unit pregnant patient population with a BMI +/=30 [77-81]. A process of optimal allocation will be undertaken [79-81]. This will involve calculation of all possible allocations and a balance statistic for each one. A proportion of all allocations with the greatest degree of balance will be identified and passed to the independent statistician on the Trial Steering Committee (TSC) blinded to unit. He will randomly select a single allocation. This will then be returned to the trial statistician. The process of optimal allocation will be carried out in two blocks of ten sites with each block allocation being chosen by the independent statistician from the 25% most optimal allocations in each case. A statistician independent of the study but within the South East Wales Trials Unit will create random numbers for intervention/control arm allocation. The rest of the trial team and the clinics themselves will be informed of allocation after site recruitment.

In the event of delayed approvals for the maternity units such that it is not possible to randomise the second block of 10 sites together, minimisation will be used. A random component will be added to the minimisation algorithm using an 80% weighted randomisation. The allocations of the first block will be used to balance the remaining sites [77,78].

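### Child weight centile is to be adjusted for birth weight, a post-randomisation variable, so the comparison gives neither the total effect on attained child weight nor that on weight gain

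*Protocol article*

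**What the plan says.** The relevant row of Table 1 (protocol article, Outcomes, secondary outcomes) reads "Child weight centile (adjusted for birth weight and age", with collection times "Birth, 6p, 6 m, 12 m".

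On timing, Site randomisation states that "Sites will be randomised when all necessary approvals are obtained". Study intervention says that group sessions are offered "from the point of recruitment (between 12 and 20 weeks gestation) up until 6 weeks postpartum".

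On why the child is studied, the Background (Obesity: the problem) links excess gestational gain to later child obesity and concludes: "This suggests there is potential for influencing the mother’s lifestyle and weight as well as the child’s weight". Obesity interventions cites a large trial of a lifestyle intervention in pregnancy in which "the intervention was associated with a reduction in the risk of birth weight above 4000 g". The corresponding item under Aim of the study is "to examine the child’s weight gain", and the text under Outcomes again speaks of the child's weight gain.

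The Quantitative analysis section gives a general rule for secondary outcomes: multilevel models with baseline scores as covariates where appropriate. It does not mention birth weight.

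**The concern.** Adjusting for a variable measured before treatment can begin is harmless and usually gains precision. Birth weight is not such a variable here. It is recorded after up to several months of exposure, and it lies on a plausible path from the intervention to the child's later weight.

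Conditioning on it has two consequences. First, any effect carried through birth weight is taken out of the comparison, so what remains is a type of direct effect. Second, birth weight and later weight may share causes that are not measured. Once birth weight is held fixed, those causes can become unbalanced between arms, and randomisation no longer protects the estimate.

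At stake is whether the trial can say what offering this programme does to the child's weight, or to the child's growth.

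**Working it through.** The plan gives no figure to reproduce on this point. The check has two parts: a comparison of the passages and an illustration.

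**Passages side by side.** Randomisation acts on sites once approvals are in place. Sessions start at 12 to 20 weeks and continue past delivery. Birth weight therefore falls after allocation and inside the intervention window. It is not a baseline score in the sense of the Quantitative analysis section.

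**Illustration.** Work in SD units with a linear path model, where T is the arm:

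- birth weight = a·T + error
- later weight = b·(birth weight) + d·T + error

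The three quantities of interest are:

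- total effect on attained weight: a·b + d
- total effect on gain (later minus birth): a·(b − 1) + d
- effect adjusted for birth weight, with no shared unmeasured cause: d

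The adjusted effect equals the first only if a·b = 0. It equals the second only if a·(b − 1) = 0. If a = 0, all three agree.

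The documents give none of a, b or d. Assumed ranges: a from -0.1 to -0.3, b from 0.3 to 0.5, and d either 0 or -0.1.

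| a | b | d | Attained, total | Gain, total | Adjusted |
|---|---|---|---|---|---|
| -0.1 | 0.3 | 0 | -0.03 | +0.07 | 0 |
| -0.3 | 0.5 | 0 | -0.15 | +0.15 | 0 |
| -0.1 | 0.3 | -0.1 | -0.13 | -0.03 | -0.10 |
| -0.2 | 0.4 | -0.1 | -0.18 | +0.02 | -0.10 |
| -0.3 | 0.5 | -0.1 | -0.25 | +0.05 | -0.10 |

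For the middle case (a = -0.2, b = 0.4, d = -0.1):

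- attained: (-0.2)(0.4) − 0.1 = -0.18
- gain: (-0.2)(0.4 − 1) − 0.1 = +0.02
- adjusted: -0.10

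The share of the attained-weight effect removed is a·b/(a·b + d). With d = -0.1 it runs from 0.03/0.13 = 23% to 0.15/0.25 = 60%. With d = 0 it is all of it.

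**Direction.** If the effect after birth runs the other way (catch-up growth), reverse the sign of d in the middle case. The total on attained weight is -0.08 + 0.10 = +0.02, while the adjusted figure is +0.10. Adjustment then overstates the effect.

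**Shared unmeasured cause.** A simulation of 400,000 children used the middle case plus an unmeasured factor acting on both weights with coefficient 0.4. The adjusted estimate was -0.07. It no longer recovers even the direct effect of -0.10.

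**The case against.** The strongest reply is that the written aim is the child's weight gain, so birth weight was probably brought in to isolate growth after birth. This stands as an account of the intention, and it rules out saying simply that the plan targets attained weight and then discards part of it. It does not rescue the method: as shown above, the adjusted comparison does not estimate the total effect on gain either.

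A second reply is that one parenthesis in a table of measurements is not a model, and might describe how the centile is derived. Age is indeed a standardising variable. But birth weight is named beside it as something adjusted for, so reading the phrase as mere centile derivation is strained.

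Third, the Background evidence on birth weight is mixed. The trial that reported fewer births above 4000 g found no effect on gestational gain and no reduction in large-for-gestational-age infants. The midwife component of the intervention also expects that fetal weight will not be harmed. This supports saying that birth weight may change, not that it will.

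A reader might infer three stronger things that the documents do not support:

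- **That the row contradicts itself because it lists birth.** The column records when measurements are taken. The primary-outcome row also lists baseline, although BMI is compared at 12 months, so birth may simply be when birth weight is collected.
- **That a real benefit would be reported as no effect.** This follows only if the benefit acts entirely through birth weight (d = 0) and shared causes add nothing.
- **That the loss is 0.03 to 0.15 z.** This is the product of two assumed ranges, 0.1 to 0.3 and 0.3 to 0.5, neither of which is in the documents.

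**Conclusion.** The point holds for this one secondary outcome. As worded, the child comparison conditions on a variable that arises after randomisation and that the intervention may alter. It therefore estimates neither the total effect on attained weight nor the total effect on gain, and it is exposed to bias from unmeasured causes common to birth weight and later weight.

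Neither size nor direction can be derived from the documents. The removal is nil if birth weight is unaffected, partial or complete if the effects before and after birth agree in sign, and can reverse if they do not. The conclusion rests on two conditions: that the adjustment enters the between-arm comparison, which is the natural reading of the row, and that an effect on birth weight is possible, which the protocol's own Background allows. The primary BMI analysis is untouched.

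**What to change.** Reword the outcome and its analysis as follows.

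1. **Main child analysis:** age- and sex-standardised weight z-score at 6 weeks, 6 months and 12 months, in the planned two-level model, with pre-randomisation or maternal baseline covariates only.
2. **Weight-gain aim:** change in z-score since birth as the dependent variable, with birth weight not on the covariate side.
3. **Birth weight:** report and compare it between arms as an outcome in its own right. Table 1 already schedules measurement of the child at birth.
4. **Any birth-weight-adjusted model:** keep it if wanted, labelled exploratory, and interpret it as a mediation analysis with its assumptions stated.

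This changes wording and analysis only. No new data are needed. The cost is some precision, because birth weight predicts later weight and would no longer be a covariate.

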### Analysis

#### Quantitative analysis

The main analysis will be by intention to treat and will compare the primary outcome of BMI at 12 months postpartum in the intervention and control groups. Multilevel modelling will be used to account for clustering within antenatal unit and individual effects. A two level linear regression model will include baseline BMI (measured at recruitment) as a covariate. Both levels will be considered ‘random effects’ i.e. patients and units are drawn randomly from a larger population of patients and units. Cluster level variables include those used to balance the randomisation: antenatal unit size; proportion of women with BMI +/=30, geographic location and ethnic mix.

For the BMI data, positively skew distributed form is anticipated and will be checked prior to analysis. Log transformation will be considered, not only to deal with the non-normality but to allow interpretation of differences between arms in percentage terms. To further aid clinical interpretation of the intervention effect, analysis of log transformed weight at 12 months postpartum will also be considered, with baseline log weight and log height as covariates. The results can then be expressed in terms of BMI or weight along with a 95% confidence interval. The intra-cluster correlation (ICC) for the primary outcome will be calculated and reported.

Intention to treat analysis will be used for all secondary outcomes. Analysis of secondary outcomes will also use multilevel modelling incorporating baseline scores as covariates where appropriate. Two level linear regression models will be used for outcomes such as pregnancy weight gain and waist-to hip ratio and validated questionnaire scores, while logistic models will be used for clinical event outcomes. 95% confidence intervals for the intervention effect will be calculated. The ICC for each secondary outcome will be calculated and reported.

The impact of individual demographic factors as well as theoretical mediators (self-efficacy, social support, intrinsic motivation and self-regulation) on the intervention effect using interaction terms included in the main analysis models will be examined. Individual demographic variables include age, ethnicity, smoking status, previous weight loss history, psychological wellbeing and social class. We also intend to carry out tests for mediator variables [97].

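### The child outcome is specified as a weight centile; the z-score from the same growth reference would be an equal-interval and modestly more efficient scale at no cost

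*Protocol article*

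**What the plan says.** In the Protocol article, Table 1 (secondary outcomes) names the child measure as "Child weight centile", in full "Child weight centile (adjusted for birth weight and age"), taken with "Calibrated baby scales and measuring tape" at birth, 6 weeks, 6 months and 12 months. The matching secondary aim is "to examine the child’s weight gain".

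The quantitative analysis section does not name this outcome when it assigns models. It states the general rule: "Analysis of secondary outcomes will also use multilevel modelling incorporating baseline scores as covariates where appropriate". It then gives two model types: "Two level linear regression models will be used for outcomes such as pregnancy weight gain and waist-to hip ratio and validated questionnaire scores", and logistic models for clinical events. A centile is continuous and is not an event, so the linear model is the one that fits.

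The article mentions no z-score (SD score) for the child. Child obesity appears only in the background: "Excess maternal weight gain during pregnancy is also associated with child obesity at 3 years and in adolescence".

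**The concern.** A centile is a z-score passed through the normal distribution function and multiplied by 100. It is bounded at 0 and 100 and it flattens towards both ends. A linear model treats one centile point as the same quantity everywhere on the scale, but in terms of weight it is not. Two infants with the same standardised change in weight contribute different amounts to the arm difference if one starts near the median and the other starts high. Adjusting for birth weight does not remove this, because the unequal spacing lies in the outcome itself.

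This matters somewhat more here than in a general infant population. The background section lists macrosomia among the risks for children of obese mothers, so the sample may sit above the reference mean, where the scale is more compressed. At stake are some precision, and an effect estimate in points that do not mean the same thing for every child.

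**Working it through.** **Inputs.** From the article: the centile scale and visits (Table 1); and, from the sample size section, 400 women analysed (200 per arm), an average of 20 per unit, and ICC 0.02. Not in the article, so assumed: child weight z-score normal with mean 0 to 1.0 and SD 1 (SD 0.9 to 1.2 as sensitivity).

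**The plan's own figure.** The only sample size is for maternal BMI. A difference of 1.5 with SD 4.5, two-sided 5% and 80% power needs 142 per arm by the normal approximation and 143 by the t-test with d = 0.333. Then 2 × 143 × 1.4 = 400.4, and 400/0.7 = 572 against the stated 570. The figure reproduces. It does not concern the child outcome; only its numbers per arm and its clustering are borrowed below.

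**1. Spacing of the scale.** Centile = 100·Φ(z). A reduction of 0.3 SD gives:
- from the median: Φ(0) − Φ(−0.3) = 0.500 − 0.382 = 0.118, or 11.8 points;
- from +1 SD: Φ(1.0) − Φ(0.7) = 0.841 − 0.758 = 0.083, or 8.3 points;
- from +2 SD: Φ(2.0) − Φ(1.7) = 0.977 − 0.955 = 0.022, or 2.2 points.

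**2. Efficiency for a shift of the whole distribution.** With z ~ N(μ, 1), the efficiency of the centile relative to the z-score for comparing means is {E[φ(z)]}² / Var[Φ(z)], where E[φ(z)] = 0.2821·exp(−μ²/4).

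| Mean z | E[φ(z)] | Var[Φ(z)] | Relative efficiency |
|---|---|---|---|
| 0 | 0.2821 | 0.0833 | 0.955 |
| 0.5 | 0.2650 | 0.0753 | 0.932 |
| 1.0 | 0.2197 | 0.0557 | 0.866 |

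Over SD 0.9 to 1.2 the ranges are 0.935–0.965, 0.914–0.941 and 0.853–0.874. The z-score does better in every case.

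**3. With adjustment for the birth value** (assumed correlation 0.4 to 0.6, simulated, each scale adjusted for its own birth value): about 0.93–0.94 at mean z 0, 0.89–0.92 at 0.5 and 0.81–0.84 at 1.0. Adjustment makes the loss slightly larger.

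**4. Power.** The design effect is 1 + 19 × 0.02 = 1.38, so 200 per arm is worth 200/1.38 = 144.9. Take a downward shift of 1/3 SD. Power = Φ(Δ / (s·√(2/144.9)) − 1.96), and √(2/144.9) = 0.1175.
- z-score: 0.3333/0.1175 = 2.84, so power is 81.0%.
- Centile, mean z 0: Δ = 9.3 points, s = 28.6, power 79.3%.
- Centile, mean z 0.5: Δ = 9.1, s = 28.1, power 79.0%.
- Centile, mean z 1.0: Δ = 7.9, s = 25.0, power 76.5%.

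The loss is 1.7, 2.0 and 4.5 percentage points. It is not adjusted for the birth value and borrows the ICC assumed for maternal BMI.

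**The case against.** The strongest reply is that Table 1 is a table of measurements, that no model is assigned to the child centile by name, and that an analysis plan not shown here may well use z-scores. It is correct that the linear model is inferred. But the scale itself is stated, not left open, and of the two model types offered only the linear one fits a continuous measure. The article also promises to check model assumptions. That would deal with the shape of residuals, but it would not make a centile point mean the same thing for every child.

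A second reply is that nothing is wrong: centiles are familiar to clinicians, are a one-to-one transform of the z-score, and do not bias a test of no difference. That stands, and it is why this is an improvement and not an error.

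Two stronger readings are tempting and should be resisted.
- A reader might infer that the centile hides the child-obesity question the trial is asking. The article states no such question. Its aim is child weight gain, follow-up ends at 12 months, there is no child-obesity endpoint or threshold, and obesity is cited only as background at 3 years and in adolescence.
- A reader might infer that reductions in the heaviest infants count for almost nothing. That needs an effect confined to the upper tail. If only the excess above z = 1 is assumed to be halved, the centile's efficiency does fall to about 0.10–0.14, but the article proposes no such effect. Even from +2 SD, a reduction of 0.3 SD is 2.2 points; the smaller figure of 1.2 points, Φ(2.3) − Φ(2.0), belongs to an increase.

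**Conclusion.** The point holds as a minor, cost-free improvement. The article specifies a scale with unequal intervals for a continuous child outcome, and a better one comes from the same growth reference. For a shift of the whole distribution the efficiency loss is about 5% at mean z 0, 7% at 0.5 and 13% at 1.0, or roughly 2 to 5 percentage points of power at 200 children per arm. These figures rest on normal z-scores with SD 1, an assumed range for the mean, and a borrowed ICC and effect size. The outcome is secondary and has no power statement. No figure in the article is wrong on this point, and the primary conclusion on maternal BMI is unaffected.

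**What to change.** In Table 1, name the child outcome as the weight-for-age z-score at each visit, from the growth reference that would have supplied the centile. In the quantitative analysis section, assign it to the two-level linear model, with the birth-weight z-score as covariate for the postnatal visits. Report centiles as descriptive summaries, for instance by converting arm mean z-scores back to centiles.

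The cost is a change of wording. No extra measurement, visit or participant is needed, because the z-score is a one-to-one transform of the centile.
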